### **B. Introduction**

Depression is a worldwide mental health problem, with a lifetime prevalence of about 20%. In Hong Kong, there are about 400-600 thousands of depressed patients with major depressive disorder (MDD) annually. However, the currently available antidepressant treatments, represented by selective serotonin reuptake inhibitors (SSRIs), are incomplete and unsatisfactory. The most apparent is the delay in the onset of action of SSRIs, which has hampered the use of this class of drugs. This is not only because the suffering of patients prolonged after commencement of treatment, but also because it leaves the patients exposed to great risk of suicide. Moreover, adverse effects which are frequently at their worst during the initial phases of treatment often result in discontinuation. Thus, the exploration of faster acting antidepressant strategies is greatly needed.

Serotonergic (5-HT) system plays a principal role in the mechanisms responsible for the slow onset of action of SSRIs. In initial phases of SSRI treatment, increased 5-HT levels in the synaptic gaps produced by reuptake blockade activate negative feedback via autoreceptors in the raphe 5-HT neurons (5-HT1A) and 5-HT projection forebrain areas (5-HT1B), resulting in a decrease in the net amount of the extracellular 5-HT by suppressing neuronal cell firing and terminal release. Repeated administration of SSRIs, however, results in the desensitization of autoreceptors, which enables 5-HT neurons to recover cell firing and leads to an increase in the extracellular 5-HT to a level higher than seen in initial treatment. Therefore, it is believed that the blockade of the negative feedback potentiates the 5-HT increase produced by SSRIs and might serve to accelerate the clinical effects of SSRIs.

Numerous studies have shown beneficial effects of electroacupuncture (EA) as additional therapy in depressed patients and the most apparent is that EA intervention remarkably shortens the latency of clinical response to SSRIs. This effect has also been confirmed in our meta-analysis and preliminary study, suggesting that EA intervention can accelerate the onset of antidepressant action. On the other hand, a large body of evidence confirms that neural effects of EA (e.g., analgesic effects) are strongly associated with the activation of the raphe 5-HT neurons. Indeed, electrophysiological and neurochemical studies have revealed that EA stimulation directly facilitates the raphe 5-HT neuronal body firing and 5-HT release in the raphe nuclei itself and the forebrain areas of mood processing. Moreover, EA stimulation inhibits the activity of 5-HT1A receptors and modulates 5-HT1B receptor and 5-HT transporter function. Our preliminary studies in patients with MDD also demonstrated that the addition of EA to paroxetine (PRX), an SSRI, significantly elevates plasma 5-HT levels in the initial phase of treatment (at week 2) and reduces the expression of platelet 5-HT1A receptors, but does not change platelet 5-HT levels, 5-HT uptake and turnover ratios, while PRX treatment alone results in an increase in the 5-HT1A expression.

These observations have led us to hypothesize that EA intervention could accelerate the clinical response to SSRIs in patients with MDD and this acceleration may be achieved

through its potentiation of 5-HT release by inhibiting autoreceptor (5-HT1A/1B) activities, uptake, and turnover. To test this hypothesis, we propose a single-blind, randomised, sham controlled study to determine relationships between the accelerating effects of EA and platelet 5-HT activities in the course of EA intervention in combination with SSRIs in patients with MDD.

The proposed project will open a new avenue towards developing faster acting antidepressant strategies from alternative medicines and provide scientific evidence to support EA as an “accelerator” used for the treatment of MDD and other psychiatric disorders associated with 5-HT. the proposed project will also bridge gaps between traditional and contemporary medicines. Two apparently innovative aspects of this application may deserve to be addressed: the development of faster acting antidepressant strategies from alternative medicines is an innovative idea and the hypothesis that 5-HT system plays a central role in antidepressant-accelerating effects of acupuncture is novel and original.

### **C. Aims and hypothesis**

The central theme of this proposed study is to test the hypothesis that EA intervention could accelerate the clinical response to SSRIs in patients with MDD. Meanwhile, we also would like to determine whether the accelerative effects of EA are achieved through its potentiation of 5-HT release by inhibiting autoreceptor (5-HT1A/1B) activities, uptake, and turnover. To test these hypotheses, a single-blind, randomised, sham controlled study is proposed to detect differences in the clinical and platelet 5-HT responses between MDD patients treated with fluoxetine (FLX, an SSRI) in combination with active and sham EA intervention. The three aims are as follows:

- (1) To determine whether the patients in active EA intervention could yield significantly greater improvements on depressive symptoms, clinical response, remission rates, and the latency to clinical response than in sham EA intervention following 3 weeks of treatment;
- (2) To compare the effects of sham and active EA intervention in combination with FLX on platelet 5-HT levels, uptake, turnover, 5-HT1A/1B receptors and 5-HT transporter (SERT) activities; and
- (3) To determine correlations between clinical measures and platelet 5-HT indices.

### **D. Plan of investigation**

Outline: This is a 3-week, single-blind, randomised, sham controlled study. A total of 70 patients with a primary diagnose of MDD will be recruited. Under single-blind condition, patients will be randomly assigned to FLX (10-30 mg/day) combined with 12 sessions of active or sham EA for 3 weeks. EA intervention of each session is conducted by electrically stimulating six pairs of acupoints for 30 min. The primary efficacy is measured using the 17-Item Hamilton Depression Rating Scale (HAMD-17), Clinical Global Impression-Severity Scale (CGI-S), and Self-Rating Depression Scale (SDS). The measures for the secondary efficacy include clinical response, remission rates, and the latency to the clinical response. Two blood samples will be collected from patients at baseline and at week 2 for the measurements of platelet 5-HT, 5-HIAA, SERT, and 5-HT1A/1B receptors using HPLC, binding assay, and immunoblotting methods. One blood sample will be collected from an additional group of healthy subjects (n = 12) as controls.

**Subjects:** Both in- and out-patients who meet all the following criteria will be eligible for the study: (1) either gender aged 25-65 years; (2) have MDD diagnosed as the DSM-IV; and (3) scores on the 17-item HAMD and CGI-S are at least 18 and 4 points, respectively. Patients who meet one of the following criteria are excluded from the study: (1) unstable medical conditions; (2) have suicidal attempts or aggressive behavior; (3) previously experienced manic, hypomanic, or mixed episode; or (4) immediate family members were or are diagnosed for bipolar or psychotic disorders; (5) treatment with investigational drugs in past 6 months; (6) alcoholism or drug abuse in past 1 year; (7) have needle phobia; or (8) had experienced acupuncture or electroacupuncture.

Since the pathogenesis of bipolar depression and its response to SSRIs are different from unipolars, it may need to be screened out. Bipolar disorder has been found to be strongly associated with first manic, hypomanic, or mixed episode, bipolar family history, and early age at onset of first major depressive episode (before 21 years). We therefore set entry age at least 25 years and the Exclusive Criteria 2-4. In addition, since previous experience of acupuncture may interfere with the blindness of EA, the subjects who have experienced acupuncture previously will be excluded.

**Estimation of sample size:** In order to ensure the power sufficient to detect EA effects, we perform estimations of sample size based on response rate and HAMD score, respectively. (1) Based on our preliminary data, showing nearly 36%-43% between the two groups at week 2-3, the proposed study is intended to detect a minimum 40% increase in clinical response rate following 2 weeks of EA intervention, with a power ( $1-\beta$ ) of 80% and a two-tailed level of  $\alpha = 0.05$ . Based on these assumptions, 28 patients per group are needed. (2) Based on our initial data, EA treatment could yield a 6-point reduction in HAMD score at week 2 compared to SSRI alone. The study is then proposed to detect a minimum 6-point difference between the two treatment groups in change in HAMD score at week 2 from baseline with a power ( $1-\beta$ ) of 80% and a two-tailed level of  $\alpha = 0.05$ . Based on these assumptions, 28 subjects per group are needed. The two estimations suggest the same sample size. Therefore, we will recruit 70 patients for the study when 20% dropouts are expected.

**Randomization and blind assignment:** Patients will be randomized to assign sham or active EA intervention in blocks of 2 subjects with strata of gender and age. Randomization will be processed by the PI using random digital table.

The study is in single-blinded manner, i.e., patients are not aware of either active or sham acupuncture treatment (see below). Apart from sham acupuncture procedure (see below), additional measures will be taken to ensure blinding condition: (1) Since all acupuncture points used in the proposed study (see below) are located in the head, patients in general could not visually detect the acupuncture procedures. Despite this, we will ask patients to close their eyes during acupuncture treatments; (2) Clinical assessors will be blind to acupuncture treatment condition of patients; (3) To avoid patients' communication and observations each other, we will use curtains to separate each bed during acupuncture treatment.

**Treatment procedures:** Both groups of patients will receive orally administered FLX for 3 weeks. FLX dose will be given at 10 mg/day for the first 3 days, 20 mg/day from the 4th day to 7th, and 30 mg/day from the second week and thereafter. This dosing regimen of FLX has been reported to yield optimal clinical outcomes. The choice of FLX is because this SSRI is the most commonly used antidepressant in Hong Kong psychiatry practices and, similar to PRX, the slow onset of FLX action has been well demonstrated

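### Blocks of two within gender and age strata, processed by the PI, make the second allocation of every pair predictable to anyone who knows the first, and the text at hand states no concealment step

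*Protocol*

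**What the plan says.** The paragraph on randomisation and blind assignment in protocol section D fixes three things.

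- **Block size and strata:** "Patients will be randomized to assign sham or active EA intervention in blocks of 2 subjects with strata of gender and age". Two is the only size given. The age cut-points, and hence the number of strata, are not stated.
- **Who runs it:** "Randomization will be processed by the PI using random digital table".
- **Who is masked:** "The study is in single-blinded manner, i.e., patients are not aware of either active or sham acupuncture treatment". In addition, "Clinical assessors will be blind to acupuncture treatment condition of patients".

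The other safeguards listed are the sham procedure, patients closing their eyes, and curtains between beds. The text at hand mentions no separate list holder, central allocation, sealed envelopes or undisclosed block size. It also does not say who enrols patients or judges eligibility.

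**The concern.** Masking and concealment protect different things. All the listed safeguards act after a patient has been assigned; none hides the next assignment from the person deciding whether, or when, to enrol that patient. In a block of two, the first allocation fixes the second, so knowing one arm is enough.

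The person giving EA learns that arm at the first session. This is an inference from the nature of the treatment: the sham procedure is not described in the text at hand, and no masking of treating staff is claimed. The PI, who processes the sequence, could know more.

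If such a person can influence enrolment, a patient can be brought forward, deferred or screened out according to expected prognosis. Some eligibility criteria leave room for judgement, such as whether a medical condition is unstable. The resulting bias enters the active-sham contrast at baseline. Blinded rating does not prevent it, and analysis cannot reliably remove it. The pairing also weakens assessor masking: a rater who learns one patient's arm and knows the pairing also learns the arm of the other patient in that pair.

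**Working it through.** **Inputs from the protocol (section D):** block size 2; strata by gender and age; 28 per group needed; 20% dropout; total 70; a 6-point HAMD difference; 80% power; two-sided 0.05.

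**Assumed, because the protocol does not give them:** the number of strata (4 or 8), the SD of HAMD change, and the size of any steering.

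**1. The plan's own figure.** 56 / (1 − 0.20) = 70. The total reproduces and is not in dispute.

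**2. Predictability of a permuted block of size 2m, all earlier arms and the block size known.**

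- Expected share of allocations fully determined = 1/(m + 1).
- Expected share guessed correctly, always guessing the arm with more places left = 1/2 + (2^(2m)/C(2m, m) − 1)/(4m).

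| Block size | Determined | Guessed correctly |
|---|---|---|
| 2 | 1/2 = 50% | 1/2 + (4/2 − 1)/4 = 75% |
| 4 | 1/3 = 33.3% | 1/2 + (16/6 − 1)/8 = 70.8% |
| 6 | 1/4 = 25% | 1/2 + (64/20 − 1)/12 = 68.3% |

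Exact enumeration of all blocks gives the same values. Simple randomisation would give 50% correct guesses.

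**3. Applied to 70 patients.** If all blocks fill, 70 × 0.5 = 35 allocations are determined, and 70 × 0.75 = 52.5 guesses are correct on average. If k strata end with a half-filled block, (70 − k)/2 are determined:

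- 4 strata, all half-filled at the end: (70 − 4)/2 = 33 (47%).
- 8 strata, all half-filled at the end: (70 − 8)/2 = 31 (44%).

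**4. Randomly varying blocks of 4 and 6, equally likely.**

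- *Guesses.* Weighting by block length, (4 × 70.8% + 6 × 68.3%)/10 = 69.3%. Guessing from the running imbalance hardly needs the block size.
- *Certainty.* Take an observer who knows the sizes are 4 or 6 but not which applies. In the first block of a stratum, a block of 4 never becomes certain. A block of 6 does so if one arm is used up by the third place (probability 2/20, leaving 3 known) or the fourth (6/20, leaving 2 known). The expected number known is 3 × 0.1 + 2 × 0.3 = 0.9 per block of 6, or 0.45 per block on average. With mean length 5 that is about 9%, against 50% for blocks of 2. Later block boundaries are themselves uncertain, so the share does not stay that high.

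**5. Illustration of consequence.** Suppose half of each arm is foreknown, foreknown active places go to patients who would do d points better, and foreknown sham places to patients who would do d points worse. The bias is then 0.5d + 0.5d = d. If only half of those places are steered, it is d/2.

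The sample-size statement implies an SD of about 6 × √(28/2) / (1.96 + 0.84) ≈ 8.0; 7.9 is used here. The standard error is 7.9 × √(2/28) = 2.11. Type I error comes from the noncentral t with 54 df and noncentrality equal to bias / 2.11.

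| Bias (HAMD points) | SD 7.9 | SD 6 | SD 10 |
|---|---|---|---|
| 0.5 (d = 1, half of places steered) | 5.6% | 6.1% | 5.4% |
| 1 (d = 1, all steered) | 7.5% | 9.4% | 6.6% |
| 2 (d = 2, all steered) | 15.4% | 23% | 11% |

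A 2-point bias is a third of the 6-point target difference.

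**The case against.** The strongest reply is that predictability is not bias. For harm to follow, one person must know the block size, know the previous arm in the stratum, and be able to affect enrolment. The protocol does not say that the PI or the acupuncturists enrol. The text at hand also breaks off in the treatment procedures, so a concealment step further on cannot be excluded.

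This stands, and it limits what can be said. A reader might infer any of the following, none of which the document supports:

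- **That allocation is shown to be unconcealed.** The document supports only that no concealment step is stated in the text at hand.
- **That the PI knows every arm at enrolment.** Processing the randomisation does not by itself mean holding the list while enrolling. If it did, far more than half of the allocations would be foreknown, which is a different scenario from the one quantified here.
- **That every second patient in order of entry is known.** The determination holds within a stratum only, and 35 is a ceiling.
- **That the trial's type I error is 7.5% or 15%.** Those figures assume that every foreknown place is steered, by an assumed amount.
- **That undisclosed varying blocks remove the predictability.** They greatly reduce certainty, but at 69.3% correct guesses they do slightly worse than fixed blocks of 6 (68.3%).

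The reply does not rescue the block size. Sealed envelopes or a central call described later would still leave the second of each pair known to anyone who had learned the first arm and the block size. Nor is this a matter for an analysis plan, because block size and the person running the randomisation are stated in the protocol itself.

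**Conclusion.** The concern holds as a design weakness fixed in the protocol. Within each gender-by-age stratum, a block of two makes the second allocation certain for anyone who knows the block size and the first arm. That covers up to 35 of 70 allocations, or at least 33 or 31 with 4 or 8 strata (assumed), and about 75% can be guessed overall. None of the stated safeguards addresses this.

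Selection bias is possible, not demonstrated, because enrolment roles are not given and the text is incomplete. Its size is unknown. Under an assumed SD of 7.9 with 28 per arm, biases of 0.5 to 2 HAMD points would raise the type I error from 5% to between about 5.6% and 15%. The predictability follows from the stated rule alone and is cheap to reduce, so it should be corrected before the first patient is randomised.

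**What to change.** Make three changes to the randomisation paragraph and keep the gender and age strata.

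1. Replace the block size of two with blocks of 4 and 6 in random order, and do not disclose the sizes to anyone who enrols, treats or rates.
2. Have the list generated and held by an existing staff member with no part in recruitment, treatment or rating, in place of the PI.
3. Release each allocation only after eligibility and baseline assessments are complete, by sequentially numbered, opaque, sealed envelopes or a central call.

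The first change is not enough alone, since guesses remain about 69% correct; the second and third supply the rest of the protection. The paragraph should also say who enrols patients.

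The cost is one revised paragraph, a set of envelopes or a telephone procedure, and looser balance. The imbalance within a stratum can reach 3, against 1 with blocks of two, and it can add across strata. With 4 strata (assumed) the worst case is 4 × 3 = 12 of 70, for example 41 against 29, which is unlikely.
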